### **Eligibility**

Patients and/or their disease must fulfill the following criteria to be enrolled in this prospective study:

1. Greater than or equal to 18 years of age.

2. One to 4 untreated metastatic brain lesions.
3. Each brain lesion must be less than or equal to 5 cm in diameter and not an optimal surgical candidate.
4. Patient must be able have an MRI of the brain for treatment planning.
5. Histologic confirmation of malignancy.
6. For patients of childbearing potential, non-pregnant state, confirmed by negative serum or urine beta-HCG within (7) days of planned radiation treatment.
7. GFR adequate for IV contrast delivery for imaging.
8. No concurrent chemotherapy.
9. Patient may have had prior therapy for brain metastasis, including radiosurgery and surgical resection at the discretion of the treating physician however only new untreated lesions will be followed on protocol.

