If new lesion(s) are identified during follow up, the patient will be considered for FFSRT on protocol at the discretion of the treating physician. These new lesions are also followed every 3 months for 1 year with MRI and are considered for local control (LC) at the 6 month time point.

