## **6.0 Statistical Considerations**

Patients will be treated based on an optimal plan derived for each patient. We plan to enroll a maximum of 35 patients. We expect to encounter 2 lesions requiring treatment per patient. The primary endpoint is lesion failure within the first 6 months based on imaging assessments for each lesion. The evaluable study population will consist of patients who reach the 6-month evaluation point for local control. We will assume that failure of a lesion is independent of failure for all other lesions. However, an exploratory analysis will be conducted to assess this assumption as evidence suggesting within patient correlation is not available in the published literature.

Patients' lesions will be followed for failure starting on day 1 of radiation treatment in 3-month intervals (+/-2 months) for up to 1-year. Patients unable to complete at least 80% of their prescribed dose will be replaced.

We plan to evaluate efficacy at the level of the lesion. However, this study will monitor futility attributable to patient benefit at the patient-level using local control in consort with the assessment criteria for lesions.

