### **6.1 Efficacy Analysis**

Efficacy will be estimated by providing the incidence of lesion failure by 6-months. Assuming we will enroll patients providing 2 lesions on average, we expect to acquire 70 lesions for the entire cohort of 35 treated patients. The information below provides the estimated boundaries of exact 95% CIs for varying sample sizes. As futility monitoring is employed at the patient-level, there is potential to terminate the trial early. We presuppose 40 lesions if the trial is stopped after the first stage, and 70 lesions if the trial runs through both stages. Details regarding the futility assessment are described below.

The sample size justification for our primary endpoint is based on the incidence of lesion failure. By assuming a 6-month incidence rate of 0.50, the bounds of the 95% exact CI will not extend beyond these limits: (0.34, 0.66) with 40 lesions provided by 20 patients. Furthermore, assuming a 6-month incidence rate of 0.50, the bounds on the 95% exact CI will not extend beyond these limits: (0.38, 0.62) with 70 lesions provided by 35 patients.

Following the description of the two-stage design below is a sample size justification based on the precision associated with 95% CIs utilizing assumptions made with patient-level data.

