### 6.3 Analysis of Study Results

Descriptive statistics will be used to explore the data for quality issues, identifying outliers, and providing summaries of data distributions. T-tests or Wilcoxon rank sum tests will be used to compare continuous variables between patient groups of interest. Categorical data will be summarized using frequencies and percentages. Chi-square or Fisher's exact tests will be used to compare categorical variables between patient subgroups of interest. The LC estimates at the patient-level and incidence of failure at the lesion-level will be reported and will be accompanied by a 2-sided exact 95% confidence interval.

Rates of local control will be estimated at each of the follow-up assessments. Intracranial progression-free survival and overall survival will be summarized using the Kaplan-Meier method. Intracranial progression-free survival will be defined as the time from enrollment to either the first observation of progressive disease in the brain or death due to any cause. For intracranial PFS, patients not experiencing a death or intracranial progression will be censored at the last tumor assessment, approximately 1 year from day 1 of the start of radiation treatment. Intracranial PFS and OS will be summarized using the Kaplan-Meier method, and the 50th percentile of the K-M distribution will determine the median intracranial PFS or OS.

Finally, the cost data will be summarized using descriptive statistics such as the mean, median, standard deviation, and range. Comparisons in cost between treatment modalities will be evaluated using a paired t-test where each patient will serve as his or her own control to determine if the cost of FFSRT is comparable to standard treatment.

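### The exact interval for the primary lesion-level failure rate ignores clustering by patient, and is too narrow if failures within a patient are positively correlated

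*Protocol*

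**What the plan says.** Protocol section 6.0 sets the unit of analysis: "The primary endpoint is lesion failure within the first 6 months based on imaging assessments for each lesion". On the number of lesions it says "We expect to encounter 2 lesions requiring treatment per patient", while the Eligibility list admits "One to 4 untreated metastatic brain lesions". Section 4.0 adds, for the 6-month assessment, lesions that appear during follow-up and are treated on protocol: "These new lesions are also followed every 3 months for 1 year with MRI and are considered for local control (LC) at the 6 month".

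On dependence, section 6.0 says "We will assume that failure of a lesion is independent of failure for all other lesions", and then: "However, an exploratory analysis will be conducted to assess this assumption as evidence suggesting within patient correlation is not available in the published literature".

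Section 6.1 justifies the sample size by the width of an exact 95% interval at a failure rate of 0.50. The limits are (0.34, 0.66) for 40 lesions from 20 patients, and "0.38, 0.62) with 70 lesions provided by 35 patients" for the full trial. Section 6.3 fixes the reported result: the patient-level local control estimate and the lesion-level failure incidence each "will be accompanied by a 2-sided exact 95% confidence interval".

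The two-stage futility rule, the test of the null hypothesis and a separate exact interval for local control (section 6.2) use the patient as the unit.

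**The concern.** An exact binomial interval on 70 lesions is valid if the 70 outcomes are independent. Here they come from 35 patients. Lesions in one patient share histology, systemic disease status, mask setup and imaging, so some positive correlation in failure is plausible. Lesions added during follow-up can enlarge the clusters further.

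The exploratory check does not settle this. The protocol names no consequence if correlation is found, and section 6.3 prescribes the exact interval without condition. The reason given for assuming independence is that no published evidence of correlation is available, which is not evidence that there is none. With about 35 patients, some contributing a single lesion, the check would also have little ability to detect a moderate correlation.

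At stake are the error bars on the primary estimate and the precision claimed for it. Section 6.2 says the trial's statistical results will be used to design and power a Phase III study, so overstated precision would carry forward.

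**Working it through.** **Inputs from the protocol.** 20 patients with 40 lesions and 35 patients with 70 lesions (6.1); planning rate 0.50 (6.1); mean of 2 lesions per patient (6.0); 1 to 4 lesions per patient (Eligibility).

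**Assumptions, not in the protocol.** Within-patient correlation (ICC) from 0.1 to 0.5. For varying counts, 40/30/20/10% of patients with 1/2/3/4 lesions, which has a mean of 2.

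**Step 1: reproduce the stated limits.** Clopper–Pearson with each lesion as one independent trial:
- 20/40: (0.338, 0.662), stated as (0.34, 0.66)
- 35/70: (0.378, 0.622), stated as (0.38, 0.62)

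Both agree, so the stated limits contain no allowance for clustering.

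**Step 2: design effect, 2 lesions per patient.** DE = 1 + (m − 1) × ICC with m = 2, so DE = 1 + ICC. Effective n = lesions / DE. For ICC 0.3, 70 / 1.3 = 53.8. The exact limits are then evaluated at rate 0.50 with the effective n:

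| ICC | DE | Effective n of 70 | Limits | Half-width | Limits, 40 lesions |
|---|---|---|---|---|---|
| 0 | 1.0 | 70 | (0.378, 0.622) | 0.122 | (0.338, 0.662) |
| 0.1 | 1.1 | 63.6 | (0.372, 0.628) | 0.128 | (0.330, 0.670) |
| 0.2 | 1.2 | 58.3 | (0.366, 0.634) | 0.134 | (0.323, 0.677) |
| 0.3 | 1.3 | 53.8 | (0.361, 0.639) | 0.139 | (0.315, 0.685) |
| 0.5 | 1.5 | 46.7 | (0.350, 0.650) | 0.150 | (0.302, 0.698) |

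Even at ICC = 1, 70 lesions count as 35 and the limits are (0.327, 0.673).

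**Step 3: varying lesion counts.** The size-weighted mean count is (0.4×1 + 0.3×4 + 0.2×9 + 0.1×16) / 2 = 5.0 / 2 = 2.5, so DE = 1 + 1.5 × ICC. At ICC 0.1, 0.3 and 0.5 this is 1.15, 1.45 and 1.75. Effective n is 60.9, 48.3 and 40.0, and the limits are (0.369, 0.631), (0.353, 0.647) and (0.338, 0.662).

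**Step 4: coverage of the planned interval.** Beta-binomial simulation, 35 patients, true rate 0.50, 40,000 runs per scenario:

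| ICC | 2 lesions each | 1–4 lesions |
|---|---|---|
| 0 | 95.8% | 96.2% |
| 0.1 | 94.9% | 94.7% |
| 0.2 | 93.4% | 93.1% |
| 0.3 | 92.5% | 91.4% |
| 0.5 | 90.3% | 88.4% |

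At a true rate of 0.25 the shortfall is similar: 93.0% and 92.1% at ICC 0.3, and 90.8% and 89.2% at ICC 0.5.

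**Step 5: does the remedy work?** In the same type of simulation, a patient-clustered variance with a t reference on 34 degrees of freedom covers about 94–95% at rate 0.50 for every ICC from 0 to 0.5. At rate 0.25 it covers about 93–94%.

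**The case against.** The strongest reply has four parts.

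- **The defect is conditional.** The protocol gives no correlation, and shared histology or setup makes one plausible without sizing it. At 0.1 the built-in conservatism of the exact interval keeps coverage at about 95%. This stands. A reader might infer that the interval is too narrow whatever the data show; the documents do not support that.
- **The planning rate of 0.50 is the widest case.** If failure were 0.25 (an assumption), 70 lesions give a half-width of 0.107 under independence and 0.122 at correlation 0.3 with 2 lesions each, which equals the planned half-width at 0.50. So the planned width could still be met at a lower failure rate. This stands for width but does not answer the loss of coverage, which persists at 0.25.
- **No trial decision uses this interval.** The rules of 11 of 20 and 25 of 35, and the separate local control interval in section 6.2, count patients. A reader might infer that clustering inflates the error rates of the go/no-go decision; it does not, because lesions are not the unit there. Those analyses also do not replace the lesion-level interval, since patient-level local control is a different quantity.
- **The assumption is disclosed and will be checked, and an analysis plan may say what follows.** Disclosure is to the protocol's credit, and detail may sit elsewhere. However, the choice of an unadjusted exact interval is made in the protocol itself, in sections 6.1 and 6.3, so it is not an omitted detail.

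**Conclusion.** The point holds in conditional form and is of moderate severity. The protocol plans and reports its primary lesion-level rate with an interval that is right under independence and too narrow under positive within-patient correlation. On the assumed range, the half-width at rate 0.50 rises from 0.122 to 0.128–0.150 with 2 lesions per patient. The loss of coverage is negligible at correlation 0.1 and material from about 0.2–0.3. These sizes rest on assumed correlations, an assumed distribution of lesion counts and a beta-binomial model; the protocol fixes none of the three. The consequence is limited to the error bars on the primary lesion-level estimate and their later use in planning a Phase III study. The point estimate, futility rule, hypothesis test and patient-level interval need no change on this account.

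**What to change.** 1. Keep the lesion-level point estimate. In section 6.3, make its primary 95% interval account for clustering by patient. Options are a cluster-robust variance with a small-sample correction or t reference, a bootstrap that resamples patients, or an exact interval adjusted by the design effect. Choose one in advance. With 35 patients none is guaranteed exactly nominal coverage.
2. Show the unadjusted exact interval as a secondary figure.
3. In section 6.1, say that (0.34, 0.66) and (0.38, 0.62) hold under independence only, and add the limits at correlations 0.1, 0.3 and 0.5.
4. Keep the exploratory estimate of the correlation as a reported result. The choice of primary interval should not depend on it.

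The cost is a change of wording and a slightly wider stated interval. No new patients or data are needed. If the correlation is in fact near zero, the clustered interval loses little: in the simulation it covered about 95% at rate 0.50 and about 94% at 0.25.

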Those having access to the data include the study PI and research team personnel. Users are authenticated against MDACC's Active Directory system. External collaborators are given access to the database once approved by the PI, with their access expiring in 6 months but renewable in 6 months increments at the request of the PI. The application is accessed through Secure Socket Layer (SSL). All protected health information (PHI) will be removed from the data when it is exported from REDCap for analysis. All dates for a given patient will be shifted by a randomly generated number between 0 and 364, thus preserving the distance between dates. Dates for each patient will be shifted by a different randomly generated number. Following publication study data will be archived in REDCap. Since study data may be useful for future research studies performed under separate IRB approved protocols, study data will be archived indefinitely in REDCap. Since REDCap is a secure electronic database with controlled access, and because patient identifiers may be needed to link study data to data from other sources under future IRB approved protocols, patient identifying information will be retained in the archived database.

Initial data collection will include for each individual patient: baseline patient demographics, histology, Karnofsky performance status (6), presence or absence of systemic metastatic disease outside the brain, controlled or uncontrolled primary cancer, number of brain metastases, size and volume of largest brain metastasis treated as well as total volume of brain disease treated, dose prescribed and dose delivered to each brain lesion, and steroid use.

Patients will be followed every three months with history, clinical examination and brain MRI for 1 year. Follow up data collection at each follow-up visit will include the following:

1. Central nervous system toxicity such as Central nervous system necrosis, based on the CTCAE version 4.0.
2. Local failure in the brain on follow-up MRI defined as follows :
  - A. At least 20% increase in sum longest distance relative to lesion size prior to radiation treatment (reference 7 describes the RANO group criteria which is slightly different and uses nadir size rather than size prior to radiation)
3. Distant failure in the brain defined as additional new brain metastatic lesion(s) outside the irradiated region.
4. Overall survival.

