## 6.2 Futility Monitoring

Futility monitoring will be conducted to stop the trial early if there is no observed benefit at the patient-level. The patient-level LC rate at 6-months will be used to monitor the trial for futility. We will estimate the LC rate at 6 months. The Green-Dahlberg two-stage design (<http://www.swogstat.org/stat/public/Help/twostage.html>) will be used to terminate the trial early for futility. The null hypothesis is that the 6-month LC rate is  $\leq 55\%$  and is not as effective as previously believed, thus requiring early termination of the trial for futility. The alternative hypothesis is that the LC rate at 6-months is clinically advantageous as demonstrated by a 6-month LC rate  $\geq 75\%$ . Hypothesis testing will be conducted using a one-sided test,  $\alpha = 0.05$ , and Type II error of 0.20. The probability of stopping at the end of Stage 1 is 0.409 if the null hypothesis is true, and the probability of stopping at the end of Stage 1 is 0.014 if the alternative hypothesis is true.

We will enroll a total of 35 evaluable patients. Initially, 20 patients will be enrolled in the first Stage of the study and evaluated for response at 6-months from day 1 of radiation treatment. If there are at least 11 patients among the first 20 who achieve LC at 6-months, then an additional 15 patients will be enrolled and evaluated. Note that the 20th patient in the first Stage must be evaluated for response prior to continuing to the second stage when less than 11 patients have experienced LC at 6-months. Finally, if there are at least 25 patients achieving LC at 6-months among all 35 patients, then we will reject H0. The statistical assessments will be used to design and appropriately power a Phase III study if warranted based on the outcomes we observe in this Phase II study.

Figure 1 Study Schema

[figure not shown]

Table 1. Description of the 2 Stage Design

|                                                                                 |                            |  |
|---------------------------------------------------------------------------------|----------------------------|--|
|                                                                                 | Study Cohort               |  |
| Null Hypothesis                                                                 | LC at 6 months $\leq 55\%$ |  |
| Alternative Hypothesis                                                          | LC at 6 months $\geq 75\%$ |  |

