#### 6.4 Safety Monitoring

Neurotoxicities are expected and manageable; however, we will monitor for unreasonably excessive grade 3 or higher neurotoxicities. To assess safety, data on neurotoxicity will be tabulated by grade for the study cohort. The neurotoxicity burden for the trial will be computed by summing the number of neurotoxicities experienced by a patient, and then dividing by the total number of patients on trial.

Neurotoxicity (NT) monitoring will be conducted independently for each study cohort. We will use the method described by Thall et al. (1995) to sequentially monitor the rate of grade 3 or higher treatment related neurotoxicities starting from day 1 of FFSRT to a patient's first follow-up assessment at 3 months. If we have reason to believe that the grade 3 or higher NT rate is more than 33%, we will terminate the FFSRT cohort. NT monitoring will occur in cohorts of size 5. We will stop the trial early if at any time the

$$\Pr(\text{rate of grade 3 or higher NT at 3 months from day 1 of FFSRT} > 33\% \mid \text{data from the trial}) > 0.90.$$

That is, given the outcomes from the patients who have already been evaluated, if we determine there is more than a 90% chance that the grade 3 or higher NT rate is greater than 33%, we will stop the trial. We will assume a beta (1,1) prior distribution for the grade 3 or higher NT rate. Therefore, the trial will be stopped for excessive toxicity if at any time one of the following boundaries is crossed:

[# of patients with grade 3 or higher NT at 3 months from day 1 of FFSRT / # of patients evaluated]

$$\geq 3/5, 6/10, 8/15, 10/20, 12/25, 14/30, 16/35$$

The operating characteristics (OCs) of this decision rule are shown in Table X and are based on 1,000 simulations for each scenario. The OCs indicate that the posterior probability of stopping the trial is 51.4% if the true grade 3 or higher NT rate at 3 months from day 1 of FFSRT- given the data, is greater than 40%.

Table X. Operating characteristics for safety monitoring rule.

| P(true) | P(stop) | p10 | p25 | p50 | p75 | p90 | Avg #
pts | Avg # tox |
|---------|---------|-----|-----|-----|-----|-----|--------------|-----------|
|         |         |     |     |     |     |     |              |           |

|      |       |    |    |    |    |    |        |       |
|------|-------|----|----|----|----|----|--------|-------|
| 0.05 | 0.001 | 35 | 35 | 35 | 35 | 35 | 34.97  | 1.692 |

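### A two-month tolerance on three-monthly visits makes adjacent windows overlap, so six-month local control can be read anywhere from month 4 to month 8

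*Protocol*

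**What the plan says.** Section 6.0 tracks lesions for failure from the first day of radiation "in 3-month intervals (+/-2 months) for up to 1-year". Section 4.0 gives the same schedule without a tolerance: "Patients will be followed every three months with history, clinical examination and brain MRI for 1 year".

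The quantities that depend on the six-month reading are fixed in time:

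- Section 6.0: "The primary endpoint is lesion failure within the first 6 months based on imaging assessments for each lesion".
- Section 6.0: "The evaluable study population will consist of patients who reach the 6-month evaluation point for local control". Section 4.0 likewise defines evaluable patients as those who complete six months of follow-up.
- Section 6.2: stage 1 patients are "evaluated for response at 6-months from day 1 of radiation treatment". The trial continues with at least 11 of 20 patients in LC and rejects the null with at least 25 of 35. The null is LC of at most 55% and the alternative LC of at least 75%.

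Section 6.4 counts grade 3 or higher neurotoxicity "starting from day 1 of FFSRT to a patient's first follow-up assessment at 3 months".

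The protocol gives no narrower window for the six-month scan. It has no rule for allocating a scan to a visit, and none for a failure first seen on a six-month scan taken after month 6.

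**The concern.** The endpoint names a fixed time, but the visit rule admits readings up to two months either side of it. A clear MRI at month 4 is within tolerance, yet it cannot show control at month 6. A failure first seen at month 8 is within tolerance, yet it may have occurred after month 6. A scan at month 4.5 can be filed under either visit, so its allocation can decide whether a patient counts as evaluable.

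Local failures accumulate, so the observed LC rate depends on when it is read. The go/no-go rules are simple counts in a single arm, with no control group in which the same timing error could cancel. The neurotoxicity count has the same weakness: its closing visit may fall at month 1 or at month 5.

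**Working it through.** **1. Windows.** Inputs from Section 6.0: visits at months 3, 6, 9 and 12 from day 1, tolerance 2 months.

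| Visit | Window (months) | Overlap with next |
|---|---|---|
| 3 | 1-5 | 4-5 |
| 6 | 4-8 | 7-8 |
| 9 | 7-11 | 10-11 |
| 12 | 10-14 | none |

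Windows are disjoint only if the tolerance is below 3/2 = 1.5 months. The last window also runs past the stated year. The 3-month window lets exposure in the neurotoxicity count differ by a factor of up to 5/1 = 5.

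**2. The plan's own figures.** Inputs from Section 6.2. Let X1 ~ Bin(20, p) and X2 ~ Bin(15, p).

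- P(stop at stage 1) = P(X1 ≤ 10): 0.4086 at p = 0.55 and 0.0139 at p = 0.75. These match the stated 0.409 and 0.014.
- P(reject) = Σ over x = 11 to 20 of P(X1 = x) · P(X2 ≥ 25 − x): 0.035 at p = 0.55 and 0.758 at p = 0.75. These are the reference values for scans exactly at month 6.

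**3. Effect of reading time.** The protocol gives no time course for failure. I assume a constant hazard, so LC(t) = LC(6)^(t/6), and insert the result as p in the rule above.

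For scans spread evenly over months a to b, independently of outcome, the mean LC is [LC(a) − LC(b)] / [h(b − a)], with h = −ln LC(6)/6. This gives h = 0.0996 at LC 55% and h = 0.0479 at LC 75%. For example, at 55% over months 4-8: (0.6713 − 0.4506)/(0.0996 × 4) = 0.554.

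| Scan timing | LC read, true 55% | P(reject) | LC read, true 75% | Power |
|---|---|---|---|---|
| All at month 6 | 0.550 | 0.035 | 0.750 | 0.758 |
| Even, months 4-8 | 0.554 | 0.039 | 0.751 | 0.763 |
| Half at 4, half at 8 | 0.561 | 0.047 | 0.753 | 0.773 |
| Even, months 4-6 | 0.609 | 0.133 | 0.787 | 0.893 |
| Even, months 6-8 | 0.499 | 0.008 | 0.715 | 0.589 |
| All at month 4 | 0.671 | 0.366 | 0.825 | 0.968 |
| All at month 5 | 0.608 | 0.131 | 0.787 | 0.892 |
| All at month 7 | 0.498 | 0.008 | 0.715 | 0.587 |
| All at month 8 | 0.451 | 0.0015 | 0.681 | 0.415 |

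**4. Lesion-level endpoint.** Section 6.1 illustrates precision at a six-month failure incidence of 0.50. Under the same assumption, the incidence read at month 4 is 1 − 0.5^(4/6) = 0.37 and at month 8 is 1 − 0.5^(8/6) = 0.60. An even spread over months 4-8 gives 1 − (0.630 − 0.397)/(0.1155 × 4) = 0.50. The pattern is the same: balance cancels and drift does not.

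**The case against.** The strongest reply is that the tolerance is symmetric and the nominal visit is month 6, so early and late scans should offset each other. This largely stands. Under the same model an even spread leaves the test almost unchanged, and even a half-and-half split between months 4 and 8 keeps rejection at 0.047, below the nominal 0.05. A reader might infer that the true type I error is 0.366 or the true power 0.415. Those figures need every patient at the same edge of the window, and nothing in the protocol points to that. A reader might also infer that timing alone carries the LC rate across the gap between 55% and 75%. It does not: the extremes stop at 67.1% and 68.1%.

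What the reply does not cover is one-sided drift. The stated tolerance permits it, and neither edge has to be reached for it to matter. Balance in the average also does not correct the status of individual patients.

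A second reply is that scan allocation is commonly left to a statistical analysis plan, which is not at hand. That is fair for allocation. But the tolerance itself is fixed in the protocol, and no later rule can recover six-month status for a failure-free patient last scanned at month 4.

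**Conclusion.** The point holds as a defect to correct, though not one that invalidates the design. The overlap, and the month 4 to month 8 reading of six-month status, follow from the stated schedule without any model. They conflict with an endpoint defined as failure within six months.

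The effect on the two-stage test depends on scan dates. It is negligible for a balanced spread (0.039 and 0.763 against 0.035 and 0.758). It is material for one-sided drift: false rejection 0.133 for months 4-6, power 0.589 for months 6-8. The single-edge values of 0.366 and 0.415 are limits, not expectations.

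These figures rest on a constant hazard and on timing unrelated to outcome, neither of which the protocol addresses. They also take visits as anchored on day 1. If the tolerance applied to each interval between visits, the second visit could fall anywhere from month 2 (1 + 1) to month 10 (5 + 5).

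**What to change.** 1. Replace the tolerance in Section 6.0 with one below 1.5 months. For example, one month gives windows 2-4, 5-7, 8-10 and 11-13. Assign each MRI to a single visit by its actual date. This also bounds the closing visit of the neurotoxicity count.
2. Keep the 11-of-20 and 25-of-35 counts. Take six-month status from the scan inside the narrowed window together with any failure documented earlier. State how a patient with no scan in the window and no earlier failure is counted for evaluability.
3. Report a supportive time-to-event (cumulative incidence) estimate of six-month lesion failure and LC from actual scan dates, so that out-of-window scans still contribute. It cannot replace the binomial counts, because the decision rules need a yes or no for each patient.

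The cost is a protocol amendment, somewhat tighter scheduling and some scans falling out of window; no extra scans are needed. A one-month tolerance removes the overlap but not the whole reading-time effect. At its edges, false rejection is still 0.131 (all scans at month 5) and power 0.587 (all at month 7), which is why step 3 is needed as well.

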## **1.0 Objectives**

### **Primary Objectives**

1. To assess the efficacy and safety of frameless fractionated stereotactic radiation therapy (FFSRT) on the treatment of solitary and oligometastatic brain metastases in the MD Anderson Houston [name] Anderson Radiation Treatment Centers in [name] Anderson affiliates and the main campus of MD Anderson, for patients unable or unwilling to undergo frame-based stereotactic radiosurgery (SRS).

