### **Secondary Objectives**

1. To assess 6-month local control, intracranial progression-free survival and overall survival.
2. To collect data on charges and reimbursements of patients treated with FFSRT to compare those charges and reimbursements if the same patients had been treated with single-fraction, frame-based Gamma Knife SRS.

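### The declared primary endpoint (6-month lesion failure) is only estimated, while the only efficacy hypothesis and success rule sit on patient-level local control under a futility heading, with no statement of which governs

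*Protocol*

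**What the plan says.** The primary objective in section 1.0 is general: "To assess the efficacy and safety of frameless fractionated stereotactic radiation therapy (FFSRT)". It names neither an endpoint nor a unit of analysis. The first secondary objective is "To assess 6-month local control, intracranial progression-free survival and overall survival", again without saying whether control is counted by lesion or by patient.

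Section 6.0 fixes the endpoint: "The primary endpoint is lesion failure within the first 6 months based on imaging assessments for each lesion". It places efficacy at the lesion level, "We plan to evaluate efficacy at the level of the lesion", and, by contrast, futility at the patient level.

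Section 6.1 describes the primary analysis: "Efficacy will be estimated by providing the incidence of lesion failure by 6-months". It adds that "The sample size justification for our primary endpoint is based on the incidence of lesion failure". The justification is one of precision: at an assumed failure incidence of 0.50, the exact 95% limits are ("0.34, 0.66) with 40 lesions provided by 20 patients", and (0.38, 0.62) with 70 lesions from 35 patients. It gives no null value, target or threshold.

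Section 6.2 and its design table put everything else on patient-level 6-month LC: H0 at or below 55%, H1 at or above 75%, one-sided alpha 0.05, Type II error 0.20, continuation at 11 or more of 20, and a final rule: "if there are at least 25 patients achieving LC at 6-months among all 35 patients, then we will reject H0".

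**The concern.** The endpoint called primary has no decision rule, and the endpoint with the decision rule is not called primary. If section 6.2 contained only the stage 1 stop, this would be a clean division of labour: estimate by lesion, stop early by patient. But a rule that rejects H0 after all 35 patients cannot stop anything early. It is an efficacy verdict. Section 6.2 itself describes the alternative as a clinically advantageous rate, which is efficacy language.

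Lesion failure and patient-level LC can point in different directions on the same data. The protocol states no precedence and does not define patient-level LC for a patient with several lesions. What is at stake is a single pre-specified answer to the efficacy question, and the basis for the phase III planning mentioned at the end of the same paragraph of section 6.2.

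**Working it through.** **1. Reproduce the plan's own figures.**
- Lesion level, Clopper-Pearson 95%: 20/40 gives (0.338, 0.662) and 35/70 gives (0.378, 0.622). Both match section 6.1.
- Patient level: 10/20 gives (0.272, 0.728) and 21/35 gives (0.421, 0.761). Both match section 6.2.
- Stage 1 stop, P(X ≤ 10 | n = 20, p): 0.409 at p = 0.55 and 0.014 at p = 0.75. Both match section 6.2.
- Final rule: P(reject) = Σ over x = 11 to 20 of P(X₁ = x)·P(X₂ ≥ 25 − x), with X₁ ~ Bin(20, p) and X₂ ~ Bin(15, p). At p = 0.55 this is 0.035, within the stated 0.05. At p = 0.75 it is 0.758, so the Type II error is 1 − 0.758 = 0.242, not 0.20. A cut-off of 24 would give 0.073 and 0.857.

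**2. Put the two levels on one scale.** From section 6.0: two lesions expected per patient, failures assumed independent. Assumption added here, because the protocol does not define it: patient LC means every treated lesion is controlled. With lesion control c and exactly two lesions, patient LC = c².
- Null: √0.55 = 0.742. Alternative: √0.75 = 0.866. Patient LC of 55% and 75% therefore corresponds to lesion control of about 74% and 87%.

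**3. Chance of rejecting H0 at given lesion failure rates.** The mix column replaces exactly two lesions by an assumed 40/30/20/10% split over 1, 2, 3 and 4 lesions (mean 0.4 + 0.6 + 0.6 + 0.4 = 2.0), with patient LC = 0.4c + 0.3c² + 0.2c³ + 0.1c⁴. Eligibility allows one to four lesions; the split itself is illustrative.

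| Lesion failure | Patient LC, two each | P(reject) | Patient LC, mix | P(reject) |
|---|---|---|---|---|
| 20% (c = 0.80) | 0.640 | 0.232 | 0.655 | 0.294 |
| 15% (c = 0.85) | 0.7225 | 0.626 | 0.732 | 0.673 |

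An observed 14/70 failures (20%) would be reported with an exact 95% interval of 0.114 to 0.313.

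**4. Sensitivity to the assumptions.**
- Within-patient correlation ρ, two lesions: patient LC = c² + ρc(1 − c). At c = 0.80, ρ = 0.2 gives 0.672 and P(reject) about 0.37; ρ = 0.4 gives 0.704 and about 0.53. The gap narrows but remains.
- If patient LC meant at least one lesion controlled, patient LC with two lesions is 1 − (1 − c)². At c = 0.80 this is 0.96 and rejection is near certain. The undefined term can thus reverse the verdict.

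**5. Possible data sets.**
- With all-lesions LC, 24/35 patients controlled does not reject H0. If each of the 11 failing patients has one failed lesion, lesion failure is 11/70 = 15.7% (exact interval 0.081 to 0.264), or about 84% control.
- In the other direction, 25/35 rejects H0. If the 10 failing patients had four lesions each and all failed, lesion failure is 40/70 = 57%. This is an extreme case, shown only to prove that the rule does not bound the primary estimate.

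**The case against.** The best defence is that the split is deliberate. Section 6.0 openly assigns efficacy to lesions and futility to patients, and estimating a primary endpoint with a confidence interval is acceptable in a single-arm phase II trial. This stands as far as it goes: lack of a threshold for lesion failure is not in itself a fault. It does not cover the final reject-H0 rule, which goes beyond the futility role that section 6.0 declares.

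Several stronger readings are tempting, and the document does not support them:
- *The primary endpoint has no sample-size basis.* It has one: section 6.1 gives a lesion-level precision justification, and it reproduces.
- *Patient-level LC is listed as secondary.* The secondary objective names no unit. It could equally mean lesion control, the complement of the primary endpoint.
- *The 25/35 rule is the only hypothesis test.* Section 6.3 also plans a paired t-test on cost and subgroup comparisons. It is the only efficacy hypothesis with a success rule.
- *The trial has two formal verdicts that can conflict.* Only one is formal. The discordance is between a verdict and an estimate that carries the primary label.
- *The protocol permits choosing the better-looking level.* No text licenses that. The protocol is silent on precedence.
- *The square relation follows from the protocol.* It also needs the all-lesions definition and exactly two lesions each, neither of which the protocol states.

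**Conclusion.** The point holds as a mismatch among rules that the protocol itself states, not as detail that could be left to an analysis plan. The primary endpoint is estimation-only. The sole efficacy hypothesis and success rule belong to patient-level LC, under a futility heading, with no link between them and no precedence.

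The size is conditional. With all-lesions LC and independence, patient LC at 20% lesion failure is about 64-66% and H0 is rejected about 23-29% of the time; at 15% lesion failure, about 63-67%. Positive correlation raises these figures, and an any-lesion definition makes rejection near certain. The figures show that discordance is plausible; they do not forecast it. Clarification is warranted because it is cheap and settles the efficacy question before data are seen.

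**What to change.** Amend sections 1.0, 6.0, 6.1 and 6.2 as follows:
- State that the efficacy conclusion rests on patient-level 6-month LC by the 25/35 rule, and name it the primary endpoint (or a co-primary that bears the decision).
- Define patient-level LC explicitly, for example as no treated lesion failed by 6 months. Without this, the ambiguity would simply move into the primary endpoint.
- Keep lesion-level failure as a supportive estimate with its exact interval.
- Separate the stage 1 futility stop from the final efficacy rule in section 6.2, and retitle that section accordingly.
- State the unit of the 6-month local control objective and move or reword it to agree with the primary.
- Report the exact power of the rule, about 0.76 at 75%, in place of the 0.80 implied by the stated Type II error.

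The cost is wording and one definition. Boundaries and patient numbers stay as they are. The downside is that the lesion-level estimate loses its sole-primary label.
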